### Procedure

Subjects will be recruited through university mailing lists. The study call will include a registration form that requests subjects to share information about their age, linguistic background, vision and language impairments, if known. Invitations are sent to subjects who conform to the study criteria (see above). Otherwise, the subjects will be thanked for their interest. Together with an invitation letter, subjects will also receive a letter reminding them about their responsibility not to spread any infections, especially COVID-19, and to respect the hygiene rules in the testing rooms.

Upon arriving at the recording room at the University of Tartu, subjects are asked to fill out and sign a consent form informing them about the risks of the study and their right to stop participating in the experiment at any time without any consequences. They will be introduced to the eye tracking method that is carried out with synchronous speech recording.

After these introductory parts, the subjects are asked to seat themselves in front of the desktop-mounted EyeLink 1000 Plus eye tracker and lean their forehead on the head support. The chin is left unsupported because the study requires subjects to speak.

Subjects will be semi-randomly assigned to the 16 lists of experimental trials such that each list will be seen five or six times. The order of the items within a block (low vs high load) is randomized. The items are subdivided into the blocks such that there is the least possibility for semantic overlap between the target and distractor items.

Once the calibration procedures are completed successfully, subjects receive a thorough explanation of their task by seeing a sample of five pictures together with a possible written description in the bottom part of the screen. They will be given an opportunity to ask as many clarification questions as needed.

The subjects’ task is to describe simple actions by mentioning all three depicted actors using either plural or coordinated NPs. Every picture is presented for 6500 ms (Fig 3). The speech recording starts at the exact moment that the picture is shown. When the task is clear, subjects will have 6 practice trials to rehearse, after which they can again ask questions. If necessary, subjects are calibrated once more before proceeding to the experiment.

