For linguistic scoring, all sentences will be tagged for a number of linguistic parameters including the syntactic structure, number of actors mentioned, names of the actors, correspondence to the intended actors and mentions of any additional noun phrases or sentence modifiers. In addition, the length of sentences and syllable scores of sentence constituents and actor names are extracted from the phonetic annotations contained in the TextGrids.

A number of exclusion criteria are defined based on the eye movements, linguistic parameters, speech onset latencies and the accuracy of the verb probe task. These exclusions are necessary for the comparability between the sentences because the conceptual planning processes during language production are tightly related to speech timing and the syntactic structures employed. Therefore, target trials will be excluded when the first fixation to the AOI occurs later than 400 ms after picture onset, or when the time delay between the two consecutive fixations is longer than 600 ms (indication of track loss). Picture descriptions of a subject will be included only when (s)he is able to remember at least one word correctly in 90% of the load trials. The final analyses will only include fluent transitive sentences. After these exclusions, additional trials will be excluded based on speech onset latencies later than three standard deviations above the grand mean. Finally, all the data from the subject will be removed when the subject’s inclusion rate after the indicated exclusions is lower than 25%. No treatment of missing data is necessary because the planned regression modelling method (LMER) [82–84] is robust to unbalanced data.

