#### Dependent variables

The dependent variables of interest are (i) speech onset latencies, (ii) duration of naming gazes, (iii) duration of naming gazes proportional to their respective speech onset latencies, (iv) the height of sentence-initial pitch peaks as indexed by F0 maxima (v) and the height of sentence-final pitch valleys as indexed by F0 minima.

First, the starts of utterances (in milliseconds) index the speech onset latencies. Second, a gaze is defined as multiple consecutive fixations directed at the AOI [72]. Gaze duration is calculated by subtracting the onset time of the first fixation directed at the AOI from the offset time of the last consecutive fixation directed to the AOI. Typically, before the speech onset, between one and five gazes occur (see Fig 5). The number of gazes usually increases together with the complexity of the visual scene. The data analysis algorithm will compare between the durations of the gazes occurring before the speech onsets and determine the gaze with the maximum duration, i.e., the longest gaze. The naming gaze is reported as missing (NA) when, in the very unlikely case of only one gaze or of two gazes of exactly the same duration, the algorithm cannot detect a gaze with the maximum duration. The longest gaze before the speech onset is called the naming gaze and submitted to further analyses together with its AOI (either agent or patient).

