#### Statistical analysis

The goal of the statistical analyses is to determine whether the scaling of sentence-initial pitch peaks in long sentences is affected by an independent effect of incrementality or by the simultaneous effects of incrementality and high mental load. As the manipulations of the factors Double Actor (agent vs patient) and Identity (same vs different) elicit short and long sentences (see in Materials), the combinations of these are reduced into a factor Sentence Length (short vs long) for the main analysis. Thus, the main analysis examines the effect of the interaction between Cognitive Load (low vs high) and Sentence Length (short vs long) on (i) the proportional duration of naming gazes at the first-mentioned actors, (ii) duration of naming gazes, (iii) the sentence-final pitch valleys, (iv) and the sentence-initial pitch peaks.

The four dependent variables (duration of naming gazes, proportional gaze durations, sentence-final F0 minima, sentence-initial F0 maxima) are modelled with separate linear mixed-effects regression analyses (LMER, as implemented in the *lme4* package in [82, 85]). All models include the interaction between Cognitive Load (low vs high) and Sentence Length (short vs long) as the fixed effect, the block and trial number as the covariate effects, and random intercepts and slopes for items and subjects. The analysis will be carried out using sum-to-zero coding of the fixed effects. To avoid the convergence issues, the models will be optimized following the procedures suggested in Bates et al. [82]. First, the continuous variables block and trial are centred and/or scaled for the statistical analyses. Second, the convergence tolerances are adjusted by applying an optimizing algorithm diverging from the standard test but which results in the converging model. Third, and only in case the previous measures do not yield the convergence of the model fit, the random effects structure will be simplified by removing the correlations term from the random effects structure. Finally, the significances of the model estimates are obtained with the help of the *lmerTest* package [86] in R [85]. The significances of the main effects and the interaction are determined at the threshold of p<0.05.

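### The 600 ms track-loss exclusion is limited neither to the pre-speech window nor to the gaze outcomes, so as written it can cost the pitch analyses valid trials

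*Protocol article*

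**What the plan says.** All of this is in the Protocol article.

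- **Pre-processing and data harvesting.** Two eye-based rules stand in one sentence, and both remove the trial itself. The first concerns a late start of viewing: "target trials will be excluded when the first fixation to the AOI occurs later than 400 ms after picture onset". The second, which is the one at issue here, applies "when the time delay between the two consecutive fixations is longer than 600 ms (indication of track loss"). This second rule names no time window, and neither rule is confined to particular outcomes.
- **Same section, rationale.** "These exclusions are necessary for the comparability between the sentences because the conceptual planning processes during language production are tightly related to speech timing". Syntax is named as a second link.
- **Same section, subject rule.** After the trial exclusions, "all the data from the subject will be removed when the subject’s inclusion rate after the indicated exclusions is lower than 25" per cent.
- **Procedure.** "Every picture is presented for 6500 ms".
- **Dependent variables.** "The longest gaze before the speech onset is called the naming gaze". Where no longest gaze can be identified, the naming gaze is set to missing. F0 maxima and minima are extracted from the pitch contour within word boundaries.
- **Statistical analysis.** The four outcomes "are modelled with separate linear mixed-effects regression analyses". Each model contains load by length, block, trial and random effects for subjects and items. None contains a gaze variable.

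**The concern.** A long gap between fixations is labelled as track loss, which is a failure of the eye recording. It matters for an outcome only if that outcome uses eye data from the time of the gap. The naming-gaze outcomes use eye data up to speech onset, and the F0 outcomes use none. A rule that removes the trial from everything, whenever the gap occurs, reaches further than the failure it is meant to catch.

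At stake is precision, mainly in the fourth analysis (sentence-initial pitch peaks), which carries the main hypothesis. Participants justifies the extra recruitment by the spontaneous task, not by eye-tracking failure. It also says that the sample is already at the limit of what is feasible, so lost trials cannot easily be replaced.

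**Working it through.** **1. Which gaps can invalidate which outcome**

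| Outcome | Source | Gap before speech onset | Gap after speech onset |
|---|---|---|---|
| Naming gaze, absolute and proportional | Gazes before speech onset | Can invalidate it | Cannot |
| Final F0 minima, initial F0 maxima | Audio within word boundaries | Cannot affect the F0 value | Cannot |

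As written, the rule removes the trial in all four cells.

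**2. The plan's allowance for lost observations**

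The article gives no figure for track loss. The nearest figure is the inflation from 60 to 84 subjects for about 33% of observations (Participants).
- 60 / (1 − 0.33) = 89.6, so 90.
- 60 × 1.33 = 79.8, so 80.
- Neither gives 84. Since 84 / 60 = 1.40, the increase offsets a loss of 1 − 60/84 = 28.6%.

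That mismatch is a separate matter. Here it shows only that the allowance is finite and was set aside for another reason.

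**3. Effect of the missing window (assumed rates)**

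From the article: 6500 ms display, and 84 × 64 = 5376 planned target trials. Assumed: a constant hazard of a gap over 600 ms, speech onset at L = 1500 to 2500 ms, and a probability p of such a gap before speech. If the rule runs over the whole display, the share of trials lost is 1 − (1 − p)^(6500/L). Each cell gives this share and, in brackets, the number of trials lost beyond a pre-speech rule.

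| p | L = 1500 | L = 2000 | L = 2500 |
|---|---|---|---|
| 2% | 8.4% (343) | 6.4% (234) | 5.1% (168) |
| 5% | 19.9% (803) | 15.4% (557) | 12.5% (402) |
| 10% | 36.7% (1433) | 29.0% (1021) | 24.0% (751) |

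The gaze models would lose the bracketed trials needlessly. The F0 models would lose the whole share. All figures are gross, because some of these trials would also fail the fluency, structure or latency criteria.

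**4. Precision of the F0 tests**

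If a share e of F0 trials is lost, the trial-level part of the standard error grows by √(1/(1 − e)). In the worst case trial noise dominates and the allowance does not cover the loss. Starting from the planned power of 0.80 (two-sided 5% assumed), power is then Φ((1.960 + 0.842)√(1 − e) − 1.960).
- e = 5%: factor 1.026, power 0.78.
- e = 15%: factor 1.085, power 0.73.
- e = 30%: factor 1.195, power 0.65.

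The article states 0.80 for the main effects and the three-way interaction, so for the load-by-length test it serves only as a starting point. Subject and item random slopes make the real fall smaller.

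**5. The 25% subject rule**

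With 64 target trials as denominator (assumed), the limit is 0.25 × 64 = 16, so a subject is removed when more than 48 trials fail for all reasons together. With independent losses, o from other causes and e from track loss in that subject, each trial is kept with probability (1 − o)(1 − e). The binomial probability of keeping fewer than 16 is:

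| Other loss o | e = 15% | e = 30% | e = 50% |
|---|---|---|---|
| 33% | below 0.0001 | 0.0001 | 0.055 |
| 60% | 0.046 | 0.25 | 0.80 |

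At o = 33%, the expected inclusion rate reaches 25% only at e = 1 − 0.25/0.67 = 63%.

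**The case against.** **The window is silent, not set to 6500 ms.** A reader might infer that the plan expressly applies the rule to the whole display. It does not. That reading comes from joining the display time in Procedure to a rule without a window. The rule shares its sentence with one anchored to the first 400 ms, and gaze is used only before speech, so a pre-speech scope may be what is meant. This stands, and it makes the figures in step 3 conditional. The text still does not say so, and stating the window costs nothing.

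**A common trial set has a stated purpose.** The exclusions are justified by comparability, and Statistical analysis reads the pitch result through incrementality. A trial with track loss before speech has no dependable planning measure. For such gaps it would therefore be too strong to call the failure irrelevant to the pitch analysis. This stands in part. It gives no cover for gaps after speech onset. Nor does the plan keep a strictly common set: a naming gaze set to missing does not take the trial out of the F0 models.

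**Whole subjects.** A reader might infer that speakers with good audio would often be removed entirely. Step 5 does not support this at moderate track loss. It becomes material only when other losses are already heavy or one subject's tracking is very poor.

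**Bias.** A reader might also suspect bias. That would need track loss to differ by load or sentence length, and the article says nothing on this.

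**Conclusion.** The point holds as a matter of precision. As written, the rule can remove valid gaze trials for gaps after speech onset and valid F0 trials for any gap, and the comparability rationale covers only part of this. The main pitch-peak test bears the cost.

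The size cannot be derived from the article, which gives neither a track-loss rate nor an expected speech onset latency. The tables rest on assumed rates, a constant hazard and independent losses. Subjects rest only the forehead and speak during the task (Procedure), so tracking may be worse during speech. If so, more of the gaps would fall outside the gaze window than a constant hazard implies, but this is an inference. The plan's gaze and pitch conclusions are not shown to be invalid. This is a cheap improvement.

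**What to change.** - Apply the 600 ms rule only from picture onset to speech onset, and say whether a gap that straddles speech onset counts.
- Apply it only to the naming-gaze models, including the exploratory gaze model.
- Keep trials that fail only this rule in the F0 models, and compute the 25% inclusion rate for the F0 data without it.
- Repeat the F0 models on the common gaze-valid trials as a sensitivity analysis, so that pitch and incrementality can still be read on the same sentences.

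The cost is a few sentences in the exclusion rules and one extra run of the F0 models. The downside is that the gaze and F0 models use slightly different trial sets. The latency cut-off is applied after the other exclusions, so the plan should also say on which set its grand mean is computed.

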### Participants

Study subjects will be recruited from the university’s students and staff through informational mailing lists at the University of Tartu in Estonia. They must be native speakers of Estonian, and between 18 and 50 years old. The upper age limit is applied because the WM capacities are known to decay in ageing speakers (see in [65]) and due to the COVID-19 pandemic, in which the older participants belong to the higher risk group. Speakers eligible for the study should have normal or corrected to normal vision (soft contact lenses included, glasses excluded), no diagnosed language impairments and normal hearing ability. Subjects will be reimbursed 5 euros for their participation in the study.

Since the experiment is designed such that samples of subjects are going to respond to samples of target trials, PANGEA web application (Power Analysis for General ANOVA designs; [79] provided an *a priori* power analysis. The PANGEA analysis (variation parameters set to PANGEA defaults) indicates that, given the small to medium effect size (d = 0.45), the recommended sample size of 60 subjects is suitable for achieving the statistical power (1-*β*) of 0.8 in the evaluation of the three main effects and the three-way interaction between the fixed effects. Due to the spontaneous nature of the task, not all of the subjects will perform expectedly on all target trials. Therefore, the number of subjects is increased by approximately 33% of observations. Therefore, the resulting sample size is 84 subjects. The estimated sample size is at the limit of the feasibility of planned phonetic analyses and the project’s timeline.

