**Fig 5 pone.0259343.g005:**
[figure not shown]
Hypothetical onset latencies (left edge of bars) and duration (widths of bars) of gazes directed to a particular area of interest (e.g., blue refers to the agent initiating and orange to the patient undergoing the action of pulling) during the description of an item ‘man pulling a donkey’ in Estonian. The numbers on the squares count the gazes. The black vertical line indicates the speech onset latency. The red ellipse highlights the gaze that is called ‘naming gaze’ and defined as a gaze of longest duration prior to the start of an utterance. For assessing the degree of incrementality, the duration of the naming gaze is divided by the speech onset latency (for similar analysis procedures and data see, e.g., [19]).

Finally, F0 maxima and F0 minima are automatically extracted within the boundaries of agent and patient names and the boundaries of sentence-final words in cases where patient names do not occur at the end of a sentence (e.g., some sentence modifier (e.g., varsti, ‘soon’) follows the patient name). F0 maxima and minima measured in hertz (Hz) will be converted into semitones relative to speaker means based on Eq (1)
$$\begin{array}{c} F0_{st}=12*log_{2}\left(\frac{F0_{Hz}}{F0_{mean}}\right), \end{array}$$
(1)
where *F*0_*mean*_ is the subject’s mean F0 aggregated over all F0 contours extracted from all of the subject’s utterances. This method of converting F0 into semitones has the benefit of partly cancelling out the large-scale, gender-based differences in voice pitch (males typically have lower voice pitch than females). The effect of sentence length on sentence-initial pitch peaks is expected to be smaller than the gender effect. When gender variation in voice pitch is included in the data, the critical effects of sentence length and WM may remain unrevealed.

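### Sentence Length is coded from the picture, but any fluent transitive sentence is admitted, so descriptions that do not match the picture condition stay in under the wrong length label

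*Protocol article*

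**What the plan says.** Under Statistical analysis, the picture factors Double Actor and Identity define the length variable: "the combinations of these are reduced into a factor Sentence Length (short vs long) for the main analysis". The exploratory analyses in the same section treat Identity and Sentence Length as the same thing. The label therefore records what the picture was meant to elicit, not what was said.

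Under Pre-processing and data harvesting, every sentence is tagged for syntactic structure and for "number of actors mentioned, names of the actors, correspondence to the intended actors and mentions of any additional noun phrases or sentence modifiers". Produced length and syllable counts are measured as well, from the phonetic labelling. The exclusions are then introduced: "A number of exclusion criteria are defined based on the eye movements, linguistic parameters, speech onset latencies and the accuracy of the verb probe task". The rules that follow concern late first fixations and track loss, word recall, speech onset latency and a minimum inclusion rate per subject. The one linguistic rule is "The final analyses will only include fluent transitive sentences".

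Materials relies on instruction and training to secure the intended length. Speakers are told to name every depicted actor, with plural noun phrases for same-identity pairs and coordinated ones for different-identity pairs. Participants nevertheless expects that "not all of the subjects will perform expectedly on all target trials".

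**The concern.** No stated rule compares the produced sentence with the picture condition. Leaving out an actor, or using one plural noun for two different actors, yields a sentence that is fluent, transitive and short, yet it enters the models as long. The reverse error, a coordinated phrase for a same-identity picture, enters as short.

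The fourth main analysis tests whether the length effect on sentence-initial pitch peaks depends on load. If speakers fall back on shorter descriptions more often under load, the contrast in produced length shrinks in the high-load block. The pitch difference then shrinks with it, even if load leaves pitch planning unchanged. The study's own theory makes this possible: The present study expects load to reduce the number of activated concepts. Mismatch that is equal in both blocks creates no interaction, but it dilutes the length effect and any true interaction. It also favours the null result sought in the third analysis, where sentence-final pitch should not depend on length.

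**Working it through.** The plan states no mismatch rate or expected length effect in semitones, so there is no figure to reproduce. The check is algebra on the coding rule, followed by assumed rates.

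**Inputs from the protocol**
- Length label: set by the picture (Statistical analysis).
- Linguistic inclusion: fluent and transitive only (Pre-processing and data harvesting).
- 64 target trials per subject (Design), so 64 / 4 = 16 per Load x Length cell.
- 84 subjects (Participants); significance threshold 0.05 (Statistical analysis).

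**Formula**
- Let D be the true pitch difference between sentences produced long and produced short, equal at both loads, and let mu be the mean for sentences produced short.
- Mean of trials labelled long: mu + (1 - mL)D.
- Mean of trials labelled short: mu + mS x D.
- Observed length effect: (1 - mS - mL)D.
- Spurious interaction, high minus low load: -[(mS + mL) at high load - (mS + mL) at low load] x D.

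**Results for assumed rates, with mS = 0**

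| mL, low load | mL, high load | Effect, low load | Effect, high load | Spurious interaction |
|---|---|---|---|---|
| 10% | 10% | 0.90D | 0.90D | 0 |
| 5% | 10% | 0.95D | 0.90D | -0.05D |
| 5% | 20% | 0.95D | 0.80D | -0.15D |
| 5% | 30% | 0.95D | 0.70D | -0.25D |

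Errors in the other direction count too. If mS falls from 5% to 0% under load while mL rises from 5% to 10%, the totals are 5% + 5% = 10% and 0% + 10% = 10%, and the spurious interaction is zero. Only a difference in the total matters.

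**What this could do to the test.** A simulation of a subject-level t-test on the interaction used 84 subjects and 16 trials per cell. It assumed 67% of trials retained, a trial SD of 2 semitones, a between-subject SD of the length effect of 0.5, and long-to-short errors only. It simplifies the planned mixed model, and its SDs, retention and error rates are not in the documents. With no true interaction, the rejection rates were:

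| mL, low vs high load | D = 0.5 | D = 1 | D = 1.5 |
|---|---|---|---|
| equal (0/0 or 10%/10%) | 4-5% | 5% | 4% |
| 5% vs 15% | 7% | 12% | 20% |
| 5% vs 25% | 10% | 31% | 56% |
| 5% vs 35% | 20% | 58% | 88% |

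If mismatched trials are excluded, mS = mL = 0 at both loads. The label then gives 1.00 x D, and this source of spurious interaction disappears.

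**The case against.** **The plan names linguistic parameters as a basis for exclusion and collects the tags.** That is so, and saying that produced length goes unrecorded would be too strong. But naming a basis does not supply a rule. The exclusions are listed in sequence, and none uses the actor or noun-phrase tags.

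**Off-target responses are treated as lost trials.** Participants enlarges the sample because of them, which suggests an intention to exclude. The written rule still admits those that are fluent and transitive.

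**Training and the fluency rule protect the label.** Speakers see worked examples, practise before the first block, and practise again with the memory task before the second. Disfluent trials are dropped. This should keep mismatch down, and practice could even lower it in the second block. The fluency rule is only partial cover: a speaker who corrects a wrong description is excluded, while one who never corrects it is kept.

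**Stronger readings a reader might infer.** One is that load will raise mismatch. The documents give no rates, so this is only possible. Another is that the artefact could not be told apart from the cognitive account. In the first predicted pattern, load also lowers peaks in short sentences, which long-to-short mislabelling cannot produce. In the second, peaks in long sentences fall to about the level of low-load short ones, so the length effect nearly vanishes, whereas the assumed rates leave 0.70D to 0.90D. The gaze analyses add separate evidence on incrementality. What stands is that a significance test of the interaction alone would not separate the two explanations.

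**Modifiers.** Dependent variables provides for pitch extraction "in cases where patient names do not occur at the end of a sentence", so sentences with a trailing modifier appear to be kept. This does not mislabel them: length is defined by noun-phrase structure, and nothing shows that modifiers differ by Identity.

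**Conclusion.** The concern holds. Followed as written, the plan analyses some sentences under a length label they do not have, and the length effect is attenuated to (1 - mS - mL)D. If total mismatch is higher under load, the length effect is further reduced under load by the difference in mS + mL times D, in the predicted direction.

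The dilution needs only some mismatch. The spurious interaction needs both a nonzero length effect and more total mismatch under high load, and the documents establish neither. Its size is therefore unknown, and the range of 0.05D to 0.25D rests entirely on assumed rates. The point still warrants a change, because it touches the main test and the remedy uses information already planned.

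**What to change.** In Pre-processing and data harvesting, restrict the main F0 and gaze analyses to fluent transitive sentences that name all depicted actors, with a plural noun phrase for same-identity pictures and a coordinated one for different-identity pictures. The planned tags, "including the syntactic structure, number of actors mentioned, names of the actors, correspondence to the intended actors", with the transcriptions, are enough to apply this.

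Report the mismatch share in each Load x Length cell. As sensitivity analyses, rerun the models on all fluent transitive sentences, once with length coded from the produced sentence and once by picture condition. These are needed because the exclusion conditions on a response that load may itself affect.

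The cost is a sentence in the exclusion rules, one table and two reruns. The downsides are some lost trials, for which the sample was already enlarged, and possible selection by load. Excluding sentences with additional modifiers is optional.
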